### Sample size calculation

Primarily, we expect the incidence of composite major complications to be decreased in the HA380 hemoperfusion group (intervention group) compared with the control group. The sample size was calculated with our preliminary results from the pilot study, in which the primary outcome was defined as the incidence of composite major complications. In this study, we included 24 patients (*n* = 12 in each group), in which 8.3% (1 out of 12) of the patients assigned to the intervention group underwent CRRT due to severe postoperative renal failure. In contrast, 33.3% (4 out of 12) patients had either one of the following outcomes: death, secondary thoracotomy, and renal failure requiring dialysis. Assuming a two-sided type I error probability (α) of 5% and type II error probability (β) of 20%, forty patients are needed in each group. Suppose 10% of patients drop out either due to changes in surgical methods or lost in follow-up, a minimum number of 44 patients in each group are needed in order to achieve statistical significance.

### Data management and quality control

A safety monitoring committee composed of cardiovascular surgeons, anesthesiologists, perfusionists, and statisticians will be set up to monitor the progress and safety of the clinical study, including adverse events and mortality. All adverse events will be recorded in the case report form with severity assessed. A team member who is not involved in grouping, surgery, and postoperative management will be assigned to summarize the data. If for any reason a subject could not adhere to the study, he or she will be removed from the study groups and the sampled data will also be abandoned. On rare occasions, some of the blood samples withdrawn before emergent surgery may not meet the requirement for lab studies (hemolysis happened during blood withdrawn, blood clotted or the sample was contaminated, etc.). Should it occur, multiple imputation will be used to handle the missing data. However, if many pieces of data are missing, or vital data are missing (such as patient outcomes), the subject will be removed from the study group. Throughout the trial, only the project leader has access to the patient’s data and make the final decision to terminate the trial. All information will be shared with the trial team upon completion of the study.

For quality control, all perfusionists and anesthesiologists will receive unitive training to ensure correct installation and operation of the HA380 hemoperfutor throughout the trial. The trial is overseen by the Ethics Committee of the 2nd affiliated hospital of Nanjing Medical University and will be audited every 6 months. All saved data will be kept confidentially in accordance with standard guidelines. All changes to the data first keyed in will be documented and a valid reason is required for data revision.

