### Randomization and blinding

On the day of surgery, the perfusionists will explain to the patient’s families the context and significance of our trials and obtain informed consents. All informed consents will be kept in a separate folder and preserved by the project leader. Upon anesthesia, a statistician who does not participate in the experiments will use a computer software to randomly designate a number of either 0 or 1 to the patient, with 0 for the control group and 1 for the intervention group. The expected number of patients in the control group will equal that of the intervention group. To keep the trial confidential, the results of random allocation will only be known to the statisticians and perfusionists. Other physicians including cardiac surgeons, anesthesiologists, intensivists, and other clinicians will be blinded to the grouping. The details of randomization will not be accessible to anyone but the statisticians and perfusionists until the end of the trial and completion of the data analysis. If exclusion criteria are met after randomization (e.g., hemi-arch replacement is performed or deep hypothermia circulatory arrest not required), the patient will be removed from the trial.

During the hospital stay, only the perfusionists are aware of the grouping of patients. First of all, the size of HA380 is small. It is often not noticeable to the surgical team. Secondly, the shape of the device is no different to conventional filters used in CPB. Therefore, it is difficult to tell if HA380 is used just by eyeballing on the CPB circuit. Third, our HA380 are specially ordered and no label is visible on the device. Thus, only the perfusionist knows if the device was used. Cardiac surgeons, intensivists, and other clinicians actively involved in the treatment of the patients are blinded to patient grouping. The detail of randomization will not be revealed until the end of the study and completion of data analysis.

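### Stated rules remove randomised patients for events after allocation, so the primary comparison is not as randomised and can be biased by an unknown amount in either direction

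*Protocol article*

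**What the plan says.** All references are to the Protocol article.

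- **Time of allocation** (Randomization and blinding): "Upon anesthesia, a statistician who does not participate in the experiments will use a computer software to randomly designate" the arm. This precedes the operation.
- **Non-adherence** (Data management and quality control): a patient who for any reason "could not adhere to the study, he or she will be removed from the study groups and the sampled data will also be abandoned".
- **Missing data** (same section): if many data are missing, or "vital data are missing (such as patient outcomes), the subject will be removed from the study group". Multiple imputation is offered only for unusable blood samples drawn before emergency surgery.
- **Exclusion criteria met after randomisation** (Randomization and blinding), with the example: "hemi-arch replacement is performed or deep hypothermia circulatory arrest not required), the patient will be removed from the trial". The list under Exclusion criteria includes a prolonged operation caused by an intraoperative accident, which cannot be known when the patient is allocated.
- **Loss allowance** (Sample size calculation): 40 per group is raised to 44 for a 10% dropout, which counts changes in surgical method together with loss to follow-up.
- **Analysis set** (Data analysis): no analysis of all randomised patients as assigned is stated.

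**The concern.** Randomisation makes the arms comparable only for the patients who were randomised. Each removal rule depends on something that happens later: adherence, the conduct of the operation, or whether an outcome was obtained. These events can be related to prognosis. A prolonged or complicated operation plausibly goes with death, secondary thoracotomy, dialysis or ECMO, all components of the primary composite. They can also be related to the arm, because the device runs in the bypass circuit during surgery. Where removal depends on both, the remaining groups differ for reasons other than treatment.

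The criteria leave room for discretion. The article sets no threshold for a prolonged operation, for failure to adhere or for many missing data. The perfusionist knows the arm and helps collect the intraoperative data, so facts that trigger removal can come from an unblinded person.

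At stake is the primary result. With 44 per arm, a few patients can move it across the significance line, and once their outcomes are not kept, nobody can tell afterwards whether that happened.

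**Working it through.** **1. The plan's own figures.** Inputs from Sample size calculation: "Assuming a two-sided type I error probability (α) of 5"%; "type II error probability (β) of 20%, forty patients are needed in each group"; pilot rates of "8.3% (1 out of 12) of the patients assigned to the intervention group" and, in the other group, "33.3% (4 out of 12) patients had either one of the following outcomes".

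Pooled two-proportion formula, with p1 = 0.333, p2 = 0.083 and mean p̄ = 0.208:

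n = [1.96·√(2p̄(1−p̄)) + 0.842·√(p1(1−p1) + p2(1−p2))]² / (p1−p2)² = [1.96×0.574 + 0.842×0.546]² / 0.25² ≈ 40.2, which rounds up to 41.

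The stated 40 is reproduced within one patient. For the dropout allowance, 40×1.1 = 44 and 40/0.9 = 44.4, so 44 to 45. The sample size is not the problem here. The 10% loss is about 4 patients per arm.

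**2. Can 4 removals per arm decide the result?** The article gives no event rates among removed patients, so what follows is assumed. Take an analysed result close to the planning rates: 13/40 control (32.5%) and 3/40 device (7.5%). Restore 4 patients to each arm. The test is the Pearson chi-squared without continuity correction, N(ad−bc)²/(product of margins).

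| Outcome of the 4 removed per arm | Control | Device | Chi-squared | p | Fisher p |
|---|---|---|---|---|---|
| As analysed, after removal | 13/40 | 3/40 | 7.81 | 0.005 | 0.010 |
| No events in either arm | 13/44 | 3/44 | 7.64 | 0.006 | 0.011 |
| All events in both arms | 17/44 | 7/44 | 5.73 | 0.017 | 0.030 |
| Events in device arm only | 13/44 | 7/44 | 2.33 | 0.13 | 0.20 |
| Events in control arm only | 17/44 | 3/44 | 12.68 | 0.0004 | 0.0007 |

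For example, the fourth row is 88×(13×37−31×7)² / (44×44×20×68) = 88×264²/2,632,960 = 2.33. Equal patterns leave the result significant. The two unequal patterns move it in opposite directions, and one of them removes significance.

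**3. One-sided against balanced removal from a weaker result.** Assume 15/44 control v 8/44 device as randomised, p = 0.089.
- Remove three events from the device arm only: 15/44 v 5/41, p = 0.017. The relative risk goes from 0.53 to 0.36.
- Remove three events from each arm: 12/41 v 5/41, p = 0.057. This does not cross 0.05.

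**4. False-positive risk in the unfavourable direction.** Assume no device effect, a true risk of 1/3 in both arms, 44 randomised per arm, k device-arm patients with events removed and no controls removed. By exact binomial enumeration, the chance of a significant result in favour of the device for k = 0, 1, 2, 3, 4 is 2.7%, 3.9%, 5.5%, 8.0% and 11.1% with chi-squared, and 1.5%, 2.7%, 4.6%, 6.9% and 9.2% with Fisher. At k = 4 the expected device-arm rate is (44/3 − 4)/40 = 26.7% instead of 33.3%. This is one chosen direction; the mirror case would work against the device.

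**5. Power.** On the planning rates, 44 per arm gives 83.5% and 40 per arm gives 79.8%, before any dilution.

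**The case against.** The strongest objection concerns direction. A reader might infer that the rules probably favour the device, since an unblinded perfusionist is close to the events that trigger removal. The article does not support that. Surgeons are blinded, so a change of operation may be unrelated to the arm. Pre- and postoperative data are collected by blinded team members, and a person outside grouping, surgery and postoperative care summarises the data. Nothing says that the perfusionist decides removals. Balanced removal, as in step 3, does much less harm. This stands: bias towards the device is possible but not shown to be likely.

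A reader might also infer that every removed patient's data are discarded. That is explicit only for non-adherence, and the article does not say whether the sampled data are blood samples alone or all data. The other rules say only that the patient leaves the trial or the study group. The prolonged-operation route is an inference from two sections read together, though a natural one. The 10% allowance names only changed surgery and loss to follow-up, so it does not measure all the routes.

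The routes are not equally serious. Removal on a surgical decision made blind to the arm threatens the comparison less than removal for non-adherence or a missing outcome. That hemi-arch repair and absence of circulatory arrest are missing from the exclusion list is untidy, but it adds nothing to the bias argument.

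Finally, a fuller protocol or analysis plan may exist. That does not answer the point, which rests on removal rules the article states. An analysis plan can redefine the analysis set, but it cannot analyse abandoned data or outcomes never collected.

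**Conclusion.** The point holds. Removal after allocation is stated for non-adherence, for missing data or outcomes, and for exclusion criteria met later. The primary comparison is therefore not as randomised. The size of the bias is unknown, and its direction is open.

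The planned loss of about 4 per arm is enough to matter: the same analysed result (p = 0.005) corresponds to anything from p = 0.13 to p = 0.0004 as randomised, depending on who was removed. Those figures rest on assumed outcomes among the removed patients and are extremes, not forecasts. The article gives nothing with which to choose between them. This should be corrected before the primary result is relied on.

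**What to change.** 1. Define the primary analysis as all randomised patients in the arm assigned.
2. Do not use the prolonged-operation criterion or a changed operation as a reason for removal after randomisation.
3. Replace the rule that removes non-adherent patients and abandons their data with one that records the deviation and continues follow-up to 30 days.
4. Keep patients with a missing outcome in the analysis set. State the missing-data method and a sensitivity analysis; multiple imputation with best-case and worst-case bounds is one acceptable choice.
5. Report any removals already made, by arm and reason.
6. Keep a per-protocol set (full arch repair, circulatory arrest performed, device used as assigned) as supportive only.

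**Cost.** This is mostly wording, at a single centre with a 30-day endpoint. Recruitment began in January 2019 and was due to end in December 2020, so 30-day outcomes for patients already removed would have to be retrieved and some may be lost. Patients without full arch repair or circulatory arrest may dilute the effect somewhat, which offsets part of the power gained by analysing 44 rather than 40 per arm.

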### Data analysis

After completion of the trial, data analysis will be done by a certified statistician with SPSS20.0 (IBM, Chicago, IL, USA). Levels of inflammatory cytokines and coagulation parameters will be expressed as mean ± standard deviation or median (interquartile range). An independent *t* test or the Wilcoxon signed-rank test will be used to check if the data is within normal distribution before analysis. Categorical variables will be analyzed with chi-squared and Fisher’s exact tests.

The relative risk of primary and secondary outcomes in the hemoperfusion group and the control group will be compared using the multivariate logistic regression. Kaplan-Meier curves and log-rank analysis will be used to compare inter-group differences in primary and secondary outcomes. When comparing the changes in coagulation factor levels during the perioperative period, the effect of hemoperfusion on coagulation factors throughout the study will be assessed using repeated measures’ analysis of variance (ANOVA) and analysis of covariance (ANCOVA). When the *p* < 0.05, the result is considered statistically significant.

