**Methods:**

This study is a single-center, randomized, controlled, double-blind clinical trial. The study aims to recruit 88 patients with ATAAD and aortic arch involvement who will undergo CPB and DHCA to repair the dissected aorta. Patients will be randomized equally into the CPB/DHCA only group (control group) and the CPB/DHCA + HA380 hemoperfusion group (intervention group), with 44 patients each. Patients in the control group will undergo CPB and DHCA only, while patients in the intervention group will undergo continuous hemoperfusion with HA380, in addition to CPB and DHCA. The primary outcome is a composite of major perioperative complications. The secondary outcomes include related inflammatory markers, coagulation parameters, and minor perioperative complications. To comprehensively evaluate the effect of hemoperfusion on the perioperative outcomes, we will also determine if there are differences in perioperative all-cause mortality, length of ICU stay, and total hospitalization costs.

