### Secondary outcome measures

Changes in the levels of plasma inflammatory factors such as IL-6, IL-8, IL-10, IL-1β, and TNF-α [time frame: up to 3 days]Changes of plasma MIF levels during the perioperative period [time frame: up to 3 days]Changes of plasma CRP levels during the perioperative period [time frame: up to 3 days]Changes of the plasma II, VII, IX, X, XI, and XII levels during the perioperative period [time frame: 2 days]Changes of the plasma APTT, PT, FIB, FDP, and DDi levels during the perioperative period [time frame: 3 days]Total drainage within the first 24 h of surgery [time frame: 24 h]Incidence of postoperative acute kidney injury [time frame: up to 30 days]: increase in serum creatinine ≥ 150% or ≥ 26.5 μmol/l from baseline [13]Incidence of postoperative respiratory failure [time frame: up to 30 days]: uninterrupted postoperative mechanical ventilation for more than 48 h [10]Incidence of postoperative delirium [time frame: up to 30 days]: we will assess delirium once a day for a total of 3 times during the first 72 h after ICU admission, using standard delirium assessments (CAM or CAM-ICU). Before the CAM-ICU will be performed, a Richmond Agitation Sedation Scale (RASS) sore should be evaluated in advance [21]Incidence of postoperative liver injury [time frame: up to 30 days]: ALT level above 150 U/l [22]Incidence of postoperative myocardial infarction [time frame: up to 30 days]: a rise and/or fall of cTn values with at least 1 value above the 99th percentile upper reference limit and at least 1 of the following:
Symptoms of myocardial ischemiaNew ischemic ECG changesDevelopment of pathological Q wavesImaging evidence of new loss of viable myocardium or new regional wall motion abnormality in a pattern consistent with an ischemic etiologyIdentification of a coronary thrombus by angiography or autopsy (not for types 2 or 3 MIs) [23]

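### The stated normality check uses two tests of location, and one of them, the Wilcoxon signed-rank test, does not suit a comparison of two unmatched arms

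*Protocol article*

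**What the plan says.** All the relevant text is in the protocol article.

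- **Data analysis, summary statistics:** "Levels of inflammatory cytokines and coagulation parameters will be expressed as mean ± standard deviation or median (interquartile range").
- **Data analysis, next sentence:** an independent t test or "the Wilcoxon signed-rank test will be used to check if the data is within normal distribution before analysis".
- **Data analysis, later:** for changes in coagulation factor levels, "the effect of hemoperfusion on coagulation factors throughout the study will be assessed using repeated measures" ANOVA, together with ANCOVA. Categorical variables get chi-squared and Fisher's exact tests. Primary and secondary outcomes are also given logistic regression and Kaplan-Meier/log-rank methods.
- **Secondary outcome measures:** the markers concerned are secondary. They include "Changes in the levels of plasma inflammatory factors such as IL-6, IL-8, IL-10, IL-1β, and TNF-α" and "Changes of the plasma APTT, PT, FIB, FDP, and DDi levels during the perioperative period".
- **Abstract, Methods:** "Patients will be randomized equally into the CPB/DHCA only group (control group) and the CPB/DHCA + HA380 hemoperfusion group (intervention group), with 44 patients each". No matching of patients is described.
- **Blood sample collection and detection:** inflammatory factors are measured at eight times, T0 to T7. The routine clotting tests (APTT, PT, FIB, FDP, DDi) and the coagulation factors (II, VII, IX, X, XI, XII) are described separately, each with its own schedule.

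**The concern.** The sentence gives two tests a job that neither can do. Placed directly after the choice between mean with SD and median with IQR, the check appears meant to decide how each marker is summarised and perhaps how it is tested. A test of location cannot guide that decision.

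The obvious repair in reading is that the authors meant a normality check, followed by a t test if it passes and a rank test if it fails. That still leaves the wrong rank test, because signed-rank is a paired or one-sample procedure and the trial compares two independent groups.

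At stake is how the cytokine results, and possibly the routine clotting results, will be compared between arms. No other sentence names a suitable method for serial cytokine concentrations. An analyst who cannot follow the sentence as written has to choose a method after the data are in.

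**Working it through.** **The plan's own figure.** The article gives no figure on this point. Its one computed figure is the sample size, which I reproduced to see whether the point touches it. Inputs (Sample size calculation): p1 = 4/12, p2 = 1/12, two-sided α = 5%, power 80%.

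- p̄ = (4/12 + 1/12)/2 = 0.2083
- n = [1.96·√(2·0.2083·0.7917) + 0.8416·√(0.2222 + 0.0764)]² / 0.25² = (1.1257 + 0.4599)² / 0.0625 ≈ 40.2, rounded up to 41 per arm

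The article states 40, where power is 79.8%; 40 × 1.1 = 44. The figure is reproduced within rounding. It rests on the binary composite, so this point does not affect it.

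**Step 1: the literal reading.** The t statistic is (x̄₁ − x̄₂)/(s·√(1/n₁ + 1/n₂)), and its null hypothesis is equal means. Two arms with the same strongly skewed distribution satisfy that null, so the test passes them about 95% of the time. Two perfectly normal arms with different means are likely to be flagged. The signed-rank test asks whether paired differences centre on zero. That too is a question of location.

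Illustration, under my assumptions and not the article's: log-normal data, SD 1 on the log scale, 40 per arm, 4,000 runs.

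| Procedure applied to log-normal data | Flags the data |
|---|---|
| Independent t test, two identical arms | 4.2% |
| Shapiro-Wilk, one sample of 40 | 99.8% |

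**Step 2: the sentence read as naming the between-arm tests.** The signed-rank statistic is the sum of the ranks of |dᵢ| over pairs with dᵢ > 0, where dᵢ = xᵢ − yᵢ. It therefore needs n₁ = n₂ and a rule saying which xᵢ belongs with which yᵢ. The rank-sum statistic counts how often xᵢ < yⱼ over all n₁·n₂ combinations and needs neither.

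- No pairing rule exists. Under Randomization and blinding, each patient is allocated individually to 0 or 1.
- Equal arms cannot be relied on. The same section removes patients who meet exclusion criteria after randomisation. Data management and quality control also removes those who cannot adhere or whose vital data are missing. With unequal arms the test cannot be computed without discarding patients.

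Under the same assumed model, with equal arms paired arbitrarily:

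| Test | Rejections, no difference | Rejections, log-shift 0.6 |
|---|---|---|
| Rank-sum | 4.6% | 73.5% |
| Signed-rank, arbitrary pairs | 4.7% | 68.0% |
| Independent t test, raw scale | 4.2% | 58.1% |

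The simulation error at 4.7% is √(0.047·0.953/4000) = 0.33 percentage points, so the type I error is compatible with 5%. The power loss is 73.5 − 68.0 = 5.5 points. In one simulated data set paired 2,000 different ways, the signed-rank p-value ran from 0.15 to 1.00, while the rank-sum p-value was fixed at 0.68.

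**Step 3: which outcomes the sentence reaches.**

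| Outcome | Method stated elsewhere | Affected? |
|---|---|---|
| Primary composite (binary) | Chi-squared/Fisher, logistic regression | No |
| Coagulation factors II to XII | Repeated-measures ANOVA, ANCOVA | No |
| Cytokines | None suited to serial concentrations | Yes |
| APTT, PT, FIB, FDP, DDi | None, unless counted as coagulation factors | Yes, on the narrow reading |

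**The case against.** The best defence is that the wording is garbled, the intention is easy to guess, and little depends on it. The sentence describes a step before analysis. The independent t test it names does suit two independent arms. Signed-rank is legitimate for within-patient change, and the outcomes are worded as changes. This is a condensed article, so the full model for serial cytokines may properly sit in an analysis plan that is not shown.

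Much of this stands, and it limits the point in four ways.

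- A reader might infer that the whole between-arm analysis of cytokines and coagulation markers is invalid. The text does not support that: the t test is suitable, and the coagulation factors have their own method.
- A reader might count tests as markers times eight sampling times, or extend the fault to every continuous outcome, such as 24-hour drainage. The article states no testing at each time point, and the preceding sentence concerns only cytokines and coagulation parameters.
- A reader might expect false positives. The simulation shows none; the harm is an order-dependent result with some loss of power.
- A reader might raise the importance because Objective and hypothesis calls cytokine differences the main purpose. The abstract and Primary outcome measures make the composite primary. That conflict is a separate matter.

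The defence does not rescue the sentence itself. Within-patient change does not answer whether the arms differ. The absence of a cytokine model could be left to an analysis plan, but a test given a purpose it cannot serve is an error in what is printed.

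**Conclusion.** The point holds in a limited form. As written, the normality check gives no information about distribution. Read as a list of between-arm tests, it is half right: the t test can stay and the signed-rank test cannot.

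The reach is secondary biomarkers only. These are the cytokines, and the five routine clotting tests if they are not meant by coagulation factors. The separate description of the two groups under Blood sample collection and detection makes that narrow reading plausible but does not settle it.

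The size is modest: about 5.5 percentage points of power at a log-shift of 0.6, with no inflation of type I error, plus a p-value that is not uniquely defined. Those figures rest on assumed log-normal data with 40 per arm and would change with other shapes or shifts. The conclusion that the tests are misapplied does not depend on them.

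**What to change.** Replace the sentence in Data analysis so that it does three things.

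1. **Distribution:** judge it by plots or a real normality assessment such as Shapiro-Wilk, or fix a log transformation in advance for the markers expected to be skewed.
2. **Comparison between arms at a single time:** use the t test or the Wilcoxon rank-sum (Mann-Whitney) test. Keep signed-rank for within-patient change only, and do not use it to compare arms.
3. **Serial markers:** extend the repeated-measures analysis already stated for coagulation factors to the cytokines and to APTT, PT, FIB, FDP and DDi, adjusted for the preoperative value. The article names ANCOVA without giving the covariate, so the new text should state it. A mixed model using all available samples is one suitable form.

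The first two items correct the error. The third is a cheap gain that also removes the doubt about whether the routine clotting tests are covered. A particular scale or a separate mixed model for each marker is not needed to put the text right.

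The cost is a few lines of text and slightly more analysis work. No sample size changes. The wording should be settled before the allocation is revealed to the analysts.

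### The plan names the relative risk as its effect measure but estimates it by multivariable logistic regression, which gives an odds ratio; with a common outcome this overstates the effect

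*Protocol article*

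**What the plan says.** The protocol article, Data analysis, gives one effect measure for the binary outcomes and one model to estimate it: "The relative risk of primary and secondary outcomes in the hemoperfusion group and the control group will be compared using the multivariate logistic regression". It mentions no log-link model, no modified Poisson model and no step that turns odds into risks. The same section plans chi-squared and Fisher's exact tests for categorical variables, and Kaplan-Meier curves with log-rank tests.

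The Sample size calculation section supplies the event rates, both from a pilot of 12 patients per group. For the intervention group it reports "8.3% (1 out of 12) of the patients assigned to the intervention group". For the comparison group it says "33.3% (4 out of 12) patients had either one of the following outcomes: death, secondary thoracotomy, and renal failure requiring dialysis". It then states "type II error probability (β) of 20%, forty patients are needed in each group", raised to 44 for dropout. The primary outcome is a ten-component composite counted up to 30 days, and each component is also a secondary endpoint (Primary outcome measures).

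**The concern.** The named measure and the named model do not match. The coefficient for treatment in a logistic model is a log odds ratio, conditional on the other covariates in the model. An odds ratio approximates a risk ratio only when the outcome is rare in both groups, and one third of controls is not rare. An odds ratio always lies further from 1 than the risk ratio for the same two risks. If the device helps, the benefit looks larger than it is; if it harms, so does the harm.

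Relative risk is the only effect measure this section names for the primary outcome. A clinician who reads 0.18 under that label would take it as an 82% reduction in the risk of a major complication. A meta-analyst could pool it as a risk ratio.

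**Working it through.** **Inputs.** Control risk p_C = 4/12 = 0.333, intervention risk p_I = 1/12 = 0.083, two-sided α 5%, power 80%, 40 evaluable per group, 44 randomised per group (Sample size calculation; abstract, Methods). The number and strength of covariates are not stated.

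**1. The plan's own figure.** With pooled variance under the null and no continuity correction:

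n = [1.96·√(2·p̄(1−p̄)) + 0.842·√(p_C(1−p_C) + p_I(1−p_I))]² / (p_C − p_I)², with p̄ = 0.208

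= [1.96·√0.330 + 0.842·√0.299]² / 0.25² ≈ 40.2, or 41 after rounding up. Power at 40 per group is 79.8%. The stated 40 is reproduced closely, so the trial was sized as a comparison of two proportions at these rates. For dropout, 40 × 1.1 = 44.

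**2. Risk ratio and odds ratio at the planned rates.**

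- RR = p_I / p_C = 0.0833 / 0.3333 = 0.25, a 75% reduction
- Risk difference = 0.333 − 0.083 = 25 percentage points
- OR = RR × (1 − p_C)/(1 − p_I) = 0.25 × 0.6667/0.9167 = 0.182, an 82% reduction in odds
- Overstatement = 81.8 − 75.0 = 6.8 percentage points. Inverted, 5.5 is printed where 4.0 is true.

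**3. Other rates.** All rows after the first are assumptions.

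| Control v intervention | RR | OR | Gap in relative reduction (points) |
|---|---|---|---|
| 33.3% v 8.3% (planned) | 0.25 | 0.18 | 6.8 |
| 20% v 5% | 0.25 | 0.21 | 3.9 |
| 33.3% v 16.7% | 0.50 | 0.40 | 10.0 |
| 33.3% v 25% | 0.75 | 0.67 | 8.3 |
| 50% v 30% | 0.60 | 0.43 | 17.1 |
| 60% v 30% | 0.50 | 0.29 | 21.4 |

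In percentage points the gap grows with the control rate. At the planned control rate it is larger for weaker effects than the pilot's.

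**4. Events.** 40 × (0.333 + 0.083) = 16.7 (13.3 in controls and 3.3 with the device), or 18.3 if all 88 patients are analysed. This count does not cause the gap in steps 2 and 3, which depends only on the two risks. It matters separately, because few events per coefficient push a fitted odds ratio away from 1: 16.7 events give 8.3 per coefficient with two coefficients, 5.6 with three and 3.3 with five.

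**5. How far adjustment could move the estimate.** This is a simulation of 3,000 trials per setting with 40 per group, marginal risks 33.3% and 8.3%, and independent normal covariates. The 2% to 5% of trials without a usable finite estimate are dropped. The number and strength of covariates are assumptions.

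| Covariates | Median fitted OR, no covariate effect (truth 0.182) | True conditional OR, log-OR 0.5 per SD | Median fitted OR, log-OR 0.5 per SD |
|---|---|---|---|
| 1 | 0.172 | 0.171 | 0.162 |
| 3 | 0.167 | 0.151 | 0.131 |
| 5 | 0.156 | 0.134 | 0.105 |
| 8 | 0.132 | 0.114 | 0.070 |

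With one covariate the shift is negligible. With five prognostic covariates, part of the move from 0.182 to 0.105 is that the conditional odds ratio is a different quantity (0.134); the rest is sparse-data bias.

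**The case against.** The strongest defence is that this is a slip of vocabulary. An adjusted odds ratio is a legitimate measure, the primary outcome also has a chi-squared or Fisher test, and an analysis plan that is not shown may tidy up the wording. Part of this stands. Those tests and the sample size rest on proportions and are untouched. The article need not list covariates, so the absence of a list is not a fault. The defence fails on the pairing itself: the article does not leave the measure open but names the relative risk and assigns it a model that does not estimate it. An analysis plan that followed the sentence would carry the error forward.

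A reader might infer more than the documents support:

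- **That the device would look about twice as effective.** Taking 0.105 for 0.25 would be a factor of 2.4, but it needs five prognostic covariates that the article does not mention. On the documents' own rates the comparison is 82% v 75%.
- **That the model is overfitted.** Its size is unknown, and with one covariate the bias is negligible.
- **That logistic regression is meant for the continuous secondary outcomes.** The same section gives repeated-measures ANOVA and ANCOVA for coagulation factors, and summary statistics with t or Wilcoxon procedures (loosely worded) for laboratory values. A sentence about relative risk is naturally read as covering binary endpoints. By listed item these are also the majority: five secondary outcomes plus ten components, against six continuous items.
- **That an empty intervention arm is a special failing of logistic regression.** The chance is (11/12)^40 = 3.1% at the planned rate, but modified Poisson then has no finite estimate either. The planned Fisher test covers that case.

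**Conclusion.** Wrong as written, of moderate severity. Followed literally, the plan would print an odds ratio under the name relative risk. At the planned rates that is 0.18 in place of 0.25, or 6.8 percentage points of relative reduction. This figure rests only on the pilot rates in the article and on an unadjusted model. In the assumed scenarios with a 50% or 60% control rate the gap is 17 to 21 points. Any further shift from adjustment with about 17 events is possible, but its size cannot be fixed from this document. The error concerns the reported effect size and its label, not the significance test of the primary outcome by chi-squared or Fisher and not the sample size.

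**What to change.** Replace the sentence in Data analysis, before the data are analysed, so that:

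- for the primary composite and the other binary outcomes, the risk ratio and risk difference are reported with 95% confidence intervals, taken directly from the 30-day proportions;
- if adjustment is wanted, the risk ratio comes from modified Poisson regression with robust standard errors, or from risks standardised from the logistic model, with few prespecified baseline covariates;
- any coefficient reported from logistic regression is labelled an odds ratio and never a relative risk;
- the sentence is expressly limited to binary outcomes, to prevent misreading.

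The cost is wording only; recruitment, sample size and the planned tests stay as they are. The downside for the sponsor is a slightly less favourable printed effect, 75% rather than 82% at the planned rates.
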